### Sample size justification

We calculate the sample size based on the chi-square test comparison of the food intolerance rate during NICU between groups. Our previous pilot study shows that the rate of food intolerance during NICU for control patients is about 85 %. We expect that the intervention group will have a reduced intolerance rate to be 75 %. With these assumptions, we will need 148 infants in each group to finish the NICU part of the study to reach 80 % power and 5 % Type I error rate. Assuming that the dropout rate to be 20 %, we will need to enroll 185 infants in each group.

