## Methods/Design

A prospective, randomized, single-center, single-blind and controlled clinical trial will be conducted in preterm children with a gestational age of less than 34 weeks meeting the inclusion criteria who cannot be breastfed. The implementer of the study will be the NICU of Zhongda Hospital Southeast University. The majority of the center’s preterm children are transferred from other hospitals in Nanjing or nearby towns, wherein most preterm children who cannot be breastfed because their mothers suffer from infectious diseases or other severe diseases requiring long-term medication are also transferred to our hospital. Most preterm children hospitalized in our hospital’s NICU can only be fed with formula. Every year, about 2,000 newborns are hospitalized in our hospital’s NICU, and preterm children with a gestational age of less than 34 weeks account for 10–15 % of the inpatients, of whom about two thirds can only be fed with formula.

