#### Primary outcome

The rates of food intolerance during NICU will be summarized and compared using the chi-square test. A *p* value <0.05 indicates a significant difference in rates between the two groups. We will also fit the logistic regression model with food intolerance status as the outcome variable, and group as the main predictor adjusting for covariates. In the case that the number of intolerance events is large enough, we will consider using a Poisson model to model the number of intolerances.

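### 148 infants per group give about 58 % power for 85 % versus 75 %, not the stated 80 %, which needs about 250 per group

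*Protocol article*

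**What the plan says.** The Sample size justification gives every input except sidedness.

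- **Test:** "We calculate the sample size based on the chi-square test comparison of the food intolerance rate during NICU between groups".
- **Control rate:** from a pilot study, "the rate of food intolerance during NICU for control patients is about 85" per cent.
- **Intervention rate:** "We expect that the intervention group will have a reduced intolerance rate to be 75" per cent.
- **Operating characteristics:** "80 % power and 5 % Type I error rate".
- **Result:** "we will need 148 infants in each group to finish the NICU part of the study to reach" those operating characteristics, raised to 185 per group for 20 % dropout. The Abstract repeats 185 per group.

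The planned analysis matches the calculation. Under Statistical analysis, Primary outcome: "The rates of food intolerance during NICU will be summarized and compared using the chi-square test", and "A *p* value <0.05 indicates a significant difference in rates between the two groups". A covariate-adjusted logistic model is mentioned there as an additional analysis.

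**The concern.** A 10-point difference between rates around 80 % is a modest effect, and 148 per group looks far too few for it. The calculation is the only justification given for the size of the trial, and it concerns the primary endpoint. If it is wrong, investigators, the ethics committee and later readers believe that the trial has a 20 % risk of missing its own target effect when the risk is about twice that. A non-significant result could then be read as evidence against a 10-point reduction that the trial was poorly placed to detect.

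**Working it through.** **Inputs** (Sample size justification): p1 = 0.85, p2 = 0.75, difference d = 0.10, mean rate 0.80, 1:1 allocation, α = 0.05, power 0.80. Two-sided is taken first, because the chi-square test in the Primary outcome section looks for a difference.

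**1. The plan's own figures.** The dropout step reproduces: 148/(1 − 0.20) = 185. The 148 does not.

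**2. Required n per group** (pooled variance under the null):

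n = [1.960·√(2·0.80·0.20) + 0.8416·√(0.85·0.15 + 0.75·0.25)]² / 0.10²

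= [1.960·0.5657 + 0.8416·0.5612]² / 0.01

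= [1.1087 + 0.4724]² / 0.01 = 249.98, so **250**.

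**3. Other ways to compute it:**

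| Method | n per group |
|---|---|
| Two-sided, unpooled | 247.2, so 248 |
| Two-sided, arcsine | 247.6, so 248 |
| Two-sided, continuity-corrected | 270 |
| One-sided 5 %, pooled | 197 |
| One-sided 5 %, unpooled | 194.8, so 195 |
| One-sided 5 %, continuity-corrected | 217 |
| One-sample against 85 %, two-sided / one-sided | 114 / 91 |

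None gives 148. A one-sided 10 % test comes near (144), but it contradicts the stated 5 %.

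**4. Power at the stated n:**

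power = Φ{[d·√n − 1.960·0.5657] / 0.5612}

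- n = 148: (1.2166 − 1.1087)/0.5612 = 0.192, power **57.6 %**. Exact binomial enumeration of the uncorrected chi-square test gives 58.0 %, or 52.1 % with continuity correction.
- n = 185, every randomised infant analysed: (1.3601 − 1.1087)/0.5612 = 0.448, power **67.3 %** (exact 67.5 %).
- One-sided 5 %: 69.5 % at 148 and 77.8 % at 185.

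**5. What 148 per group can detect.** With 85 % in controls, two-sided power reaches 80 % when the intervention rate is about 71.6 %, a drop of 13.4 points.

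**6. The corrected size against the site's capacity.** 250/0.80 = 312.5, so 313 per group or 626 in total. The opening of Methods/Design gives about 2,000 admissions a year, 10–15 % of them below 34 weeks, "of whom about two thirds can only be fed with formula". That is 2,000 × 0.10 × 2/3 ≈ 133 to 2,000 × 0.15 × 2/3 = 200 a year, or about 400–600 over the three planned years, before the other eligibility criteria and consent. The corrected total exceeds the whole range.

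**7. What a stratified test could add (illustrative).** The protocol gives no rates by gestational age, so these are assumptions. Each set averages to about 85 % versus 75 %.

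| Assumed control rates in the two strata | Assumed intervention rates | Split | Power at 148 | Power at 185 |
|---|---|---|---|---|
| 95 %, 75 % | 89 %, 61 % | 50:50 | 62 % | 71 % |
| 97 %, 70 % | 92 %, 54 % | 56:44 | 65 % | 74 % |

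**The case against.** The arithmetic itself cannot be defended. The best case on the other side concerns how it is read and what follows from it.

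- **Sidedness is not stated and the primary objective is directional.** This is true, and 58 % is a two-sided figure. The one-sided reading gives 69.5 %, so it does not rescue the claim.
- **The wrong number may be a rate rather than the n.** Pairs such as 85 % versus 71.6 % (148 per group) or 87.6 % versus 75 % (150 per group) come close to the plan's figure. This stands: the document does not show which input was intended, and the sponsor has to say.
- **67 % at 185 per group is a ceiling.** It needs an outcome for every infant and the full 10-point effect. The exclusion list under Recruitment of participants removes infants for events after feeding begins, including death, change of formula and early discharge. If the 20 % otherwise lost showed no difference (an assumption), the overall difference would shrink to 8 points and power at 185 would be about 50 %. This stands.
- **The gain from stratifying rests on assumed rates.** It also does not reach 80 %, even combined with analysing everyone. Both points stand, so stratification is an option and not part of the correction.
- **Enrolling more is ruled out only for one site within three years.** This also stands. Extending recruitment or adding a site is for the sponsor to weigh.

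**Conclusion.** The sample-size statement is wrong as written. For 85 % versus 75 % at a two-sided 5 % level, 148 per group give about 58 % power, and 80 % power needs about 250 per group, so the stated number is about 41 % short (102/250). The error carries into the enrolment target of 185, which should have been 313. The result rests only on the plan's own rates, error level and test. The one assumption is two-sidedness, and dropping it still leaves 148 well below the 197 required. A transcription fault is unlikely, because 148/0.8 equals 185 exactly and the Abstract repeats 185. It must be corrected, because it misstates what a null primary result would mean.

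**What to change.** **Correct the paragraph.** State the sidedness of the test and say which input was mis-stated. If the rates and the n are both to stand, restate the power: 148 evaluable infants per group give about 58 % for 85 % versus 75 % (two-sided 5 %), at most about 67 % if all 185 are analysed, and 80 % only if the intervention rate falls to about 71.6 %. If 80 % power for a 10-point difference is to stand, the target is 250 evaluable and 313 enrolled per group. The site's own figures do not support that within the planned period.

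**Optional, to recover part of the power without more infants:**

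- Analyse all 370 randomised infants for the primary outcome. This has to be reconciled with the post-enrolment exclusions.
- Make the decision test a Mantel-Haenszel or logistic test stratified by gestational age (below 32 versus 32 to below 34 weeks) in place of the crude chi-square. Gestational age is already collected and largely determines the feeding method in Stage I.

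Under the assumed strata above, the two together give roughly 71–74 %, so neither should be presented as restoring 80 %.

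**Cost.** Restating the power takes a few sentences and makes the stated figure less favourable. The optional steps change the analysis set and the primary test of a trial that began enrolling in November 2014 and in which clinicians know the allocation. They need a dated amendment, made before any outcome comparison by group.

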### Statistical analysis

#### Preliminary analysis

Patients’ characteristics will be summarized using mean ± SD for continuous variables and frequency (percentage) for categorical variables by groups. Continuous variables will be transformed if there is a normal assumption violation.

#### Primary outcome

The rates of food intolerance during NICU will be summarized and compared using the chi-square test. A *p* value <0.05 indicates a significant difference in rates between the two groups. We will also fit the logistic regression model with food intolerance status as the outcome variable, and group as the main predictor adjusting for covariates. In the case that the number of intolerance events is large enough, we will consider using a Poisson model to model the number of intolerances.

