### Stage I: NICU stay

Feeding timePreterm children without obvious high-risk factors are fed within 24 hours after birth.The feeding of preterm children with birth weight <1000 g, obvious history of asphyxia at birth (Apgar score ≤5), severe infection (sepsis, purulent meningitis, etc.), severe pneumonia or neonatal respiratory distress syndrome (NRDS) requiring intubation and mechanical ventilation should be postponed to 24–72 h after birth according to the situation.During the period when full enteral nutrition is not achieved, partial parenteral nutrition is given according to the daily amount of fluid and energy required by the children; when the children experience feeding intolerance and necrotizing enterocolitis and need to be fasting, complete parenteral nutrition is given; after the conditions are stable, the children gradually switch to enteral nutrition and are fed until discharge or transfer into DRI.Children in the two groups are fed with ordinary formula after discharge or transfer to DRI.Feeding methodsFor preterm children with a gestational age of <32 weeks, since their sucking-swallowing action is uncoordinated and respiratory function is not maturely developed, the children are given tube feeding (nasogastric tube or orogastric tube) using the intermittent infusion feeding method. Every time before feeding, the stomach contents are drawn to learn about gastric residual volume (GRV) and nature.Children suspected of suffering from gastroesophageal reflux or delayed gastric emptying are fed by adopting intermittent/continuous infusion feeding method with an infusion pump.Preterm children with a gestational age of 32–34 weeks are given direct bottle feeding.Children with weak sucking ability yet normal gastric emptying are given bottle feeding first, and then the remaining milk is given by tube feeding.Children with nasal continuous positive airway pressure (nCPAP) or intubation and mechanical ventilation are given tube feeding;During tube feeding or fasting period, the children are given non-nutritive sucking (NNS).Feeding milk volumeInitial feeding milk volume: according to birth weight, the children are fed from different initial milk volume once every two hours, as shown in Table 2.The milk volume begins to increase in the absence of feeding intolerance in 24-h observation, and the rates for milk increasing are shown in Table 2.

**Table 2 Tab2:** Initial feeding milk volume and increasing rate in the two groups of preterm children

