
Children in line with any of the following six criteria can be diagnosed with feeding intolerance:Gastric residual liquid >50 % of the amount of previous feedingVomiting ≥3 times/day, or the vomitus is bile-likeGastric residual liquid or vomitus is bile-like or coffee grounds-likeAbdominal distension (abdominal girth is increased by ≥1.5 cm within 24 hours, with intestinal type), and abdominal distension caused by the use of nCPAP should be ruled outRequired fasting >2 mealsBlood in the stool or fecal occult blood positive, but it is required to rule out NEC based on the general conditions, blood indicators and abdominal X-ray examination of children

Clinical treatments:Amount of gastric residue: for children with tube feeding, draw the residual milk in the stomach every time before feeding.If birth weight is <1500 g, and gastric residue is <2 ml or if birth weight is ≥1500 g and gastric residue is <3 ml or gastric residue is <30 % of the amount of previous feeding, continue feeding and closely observe.If gastric residue is 30–50 % of the amount of previous feed, reduce the amount of feeding.If gastric residue is >50 % of the amount of previous feeding, fast for one meal, and continue feeding by the original feeding plan after the condition is improved.If there is bile-like or coffee grounds-like liquid in the gastric residual liquid or vomitus, stop feeding.Abdominal distension: measure the abdominal girth at fixed parts every time before feeding. If the abdominal girth is increased by ≥1.5 cm, reduce the amount of feeding or fast for one meal, and continue feeding by the original feeding plan after the abdominal distension condition is improved.If daily vomiting occurs >3 times, do not increase the milk volume or reduce the amount of feeding.In the event of blood in the stool or fecal occult blood positive, stop feeding.2.Diagnostic and treatment reference criteria for necrotizing enterocolitis (NEC) [50] are shown in Table 3.

**Table 3 Tab3:** Modified Bell staging criteria for neonatal necrotising enterocolitis

Staging	Systemic symptoms	Gastrointestinal symptoms	Radiological signs	Treatment
IA Suspected NEC	Temperature instability, apnoea, bradycardia, lethargy	Gastric retention, mild abdominal distension, fecal occult blood positive	Normal or intestinal dilation, mild ileus	Absolute fasting, gastric decompression, antibiotic therapy for 3 days, waiting for pathogen culture results

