### Collection of clinical data during the NICU stay

Collection of general data of the objects of study:Sex, gestational age, birth weight, birth head circumference, birth body length, mode of delivery, 5-minute Apgar score, etc., of preterm childrenMother’s pregnancy complications and comorbidities: premature rupture of membrane >24 hours, placental abruption, chorioamnionitis, pregnancy-induced hypertension syndrome, preeclampsia, gestational diabetes, hyperthyroidism, hypothyroidism, systemic lupus erythematosus, kidney disease, cholestasis, acute liver failure, syphilis infection, etc.Special treatment: nasal continuous positive airway pressure (nCPAP), intubation and mechanical ventilation (MV), use of pulmonary surfactant (PS), thoracentesis, bone marrow biopsy, thoracic drainage, peritoneal dialysis, etc.Collection of case data during the NICU stay:

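### The deciding primary test ignores gestational age, although adjusting for it would cost nothing and give equal or better power

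*Protocol article*

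**What the plan says.** **Deciding test.** Under Primary outcome: "The rates of food intolerance during NICU will be summarized and compared using the chi-square test". The decision rule follows directly: a p "value <0.05 indicates a significant difference in rates between the two groups".

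**Supplementary model.** The same section adds: "We will also fit the logistic regression model with food intolerance status as the outcome variable, and group as the main predictor adjusting for covariates". It does not name the covariates.

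**Sizing.** Sample size justification uses the same crude comparison: "We calculate the sample size based on the chi-square test comparison of the food intolerance rate during NICU between groups". It takes a control rate of 85 % from a pilot, expects 75 % on the intervention, and arrives at 148 evaluable and 185 enrolled infants per group.

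**Feeding route.** Under Stage I: NICU stay, infants below 32 weeks are tube-fed, whereas "Preterm children with a gestational age of 32–34 weeks are given direct bottle feeding". Exceptions follow: nCPAP or ventilation leads to tube feeding, infants who suck weakly receive the rest of the feed by tube, and suspected reflux or delayed emptying leads to pump infusion.

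**Residuals.** The instruction on gastric residue reads: "for children with tube feeding, draw the residual milk in the stomach every time before feeding". One of the six intolerance criteria rests wholly on residual volume, and another rests on bile-like or coffee-ground residual or vomitus. Meeting any one criterion makes an infant a case.

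**Balance and data.** Randomization and blinding describes random numbers in sealed envelopes and mentions no stratification factor. The baseline data to be collected include "Sex, gestational age, birth weight, birth head circumference, birth body length".

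**The concern.** Gestational age is a plausible predictor of the ever/never intolerance endpoint for two reasons that the article itself supplies. The Background says that gut function is less mature the younger the infant, and links this immaturity to feeding intolerance. The Stage I rules also make residual measurement routine in tube-fed infants, who are mainly the younger ones.

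When a baseline variable predicts the outcome, a test that conditions on it usually has more power, and its estimate is less exposed to whatever imbalance the randomisation happens to produce. The plan collects the variable and intends an adjusted model, but leaves the decision to the test that does not use it. What is at stake is some power, and the credibility of the estimate if the arms differ by chance in the share below 32 weeks.

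**Working it through.** **Inputs from the article:** 85 % and 75 %; 5 % type I error; 80 % power; 148 evaluable per arm; 20 % dropout; 1:1 allocation. A two-sided test is assumed, since the rule speaks of a difference.

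**Inputs not in the article (assumed):** the share of infants below 32 weeks and the intolerance rate in each gestational-age stratum.

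**Step 1: the plan's own figure.** With mean rate 0.80,

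n = [1.96·√(2·0.80·0.20) + 0.8416·√(0.85·0.15 + 0.75·0.25)]² / 0.10²
= [1.1087 + 0.4724]² / 0.01 ≈ 250 per group.

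A one-sided test gives 197. The stated 148 is not reproduced either way. The dropout step is right: 148/0.8 = 185.

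**Step 2: chi-square power at 148 per arm.**

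Φ{[0.10·√148 − 1.96·√0.32] / √0.315} = Φ{(1.2166 − 1.1087)/0.5612} = Φ(0.192) ≈ 57.6 %.

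**Step 3: effect of stratifying.** 40,000 simulated trials per row compare the chi-square with a Cochran–Mantel–Haenszel (CMH) test over two strata (below 32 weeks, 32–34 weeks), with simple randomisation. Marginal rates are held at 85 % and 75 %, and a common treatment odds ratio is solved for within strata. The gestational-age odds ratio follows from the assumed control rates; for example, 95/75 % gives (0.95/0.05)/(0.75/0.25) = 6.3.

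| Assumed control rates, <32 / 32–34 weeks | Share <32 weeks | Gestational-age odds ratio | Chi-square power | CMH power |
|---|---|---|---|---|
| 85/85 % | 50 % | 1 | 58 % | 58 % |
| 90/80 % | 50 % | 2.25 | 58 % | 59 % |
| 95/75 % | 50 % | 6.3 | 58 % | 62 % |
| 97/73 % | 50 % | 12.0 | 58 % | 65 % |
| 97/67 % | 60 % | 15.9 | 58 % | 68–69 % |

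Type I error is about 5 % for both tests in every row. The share below 32 weeks matters too: at an odds ratio of 8, CMH power is 61 %, 64 % and 65 % for shares of 30 %, 50 % and 70 %.

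**Step 4: chance imbalance.** Under simple randomisation, the SD of the between-arm difference in the share s below 32 weeks is √(2·s(1−s)/n). At s = 0.5 and n = 148 this is √(0.5/148) = 5.8 points; at s = 0.6 it is 5.7 points. One SD shifts the crude difference by the SD times the gap between strata: 0.058 × 20 = 1.2 points, or 0.057 × 30 = 1.7 points. For scale, the standard error of the crude difference is √(0.85·0.15/148 + 0.75·0.25/148) = 4.6 points.

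**Step 5: can the data carry the adjusted model?** The scarcer outcome is no intolerance: 0.15·148 + 0.25·148 ≈ 22 + 37 = 59 infants. That is enough for group plus two covariates.

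**The case against.** The strongest case against is that nothing here is invalid. Under randomisation the chi-square keeps its type I error, and it matches the test used for sizing. An adjusted estimate will be reported beside it, and naming covariates is commonly left to an analysis plan. All of that stands, and it makes this a recommendation and not the repair of a defect. What remains is that the article does settle which analysis decides, and picks the one that cannot gain from gestational age.

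Four stronger readings are tempting, and the documents do not support them.

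- *Imbalance would bias the primary result.* It would not. The shifts in Step 4 are already part of the 4.6-point standard error; they cost precision and do not distort the test.
- *Substantial power is being lost.* That depends on a prognostic strength the article does not report. With no or weak association the gain is 0 to 1 point; gains of about 7 to 10 points need odds ratios of 12–16.
- *Gestational age fixes the route and decides which criteria can be met.* It sets only the default, and the exceptions may not be rare, since the Background places coordinated nutritive sucking at 34–35 weeks. Vomiting, bilious or coffee-ground vomitus, distension, fasting and blood in the stool can all be met by bottle-fed infants.
- *Adjustment would rescue the power.* Even the most favourable row stays below 70 %.

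**Conclusion.** The point holds as a free improvement. The deciding test is unadjusted, a plausible predictor is already collected, no stratification is mentioned, and the adjusted model has only a supporting role. At 148 per arm, making the adjusted test primary changes power from about 58 % to between 58 % and 69 %, with the upper end reached only under very strong assumed associations. In these settings it never costs more than simulation noise, and type I error is unaffected. The gap to 80 % comes from the sample size (about 250 per group needed) and has to be dealt with separately.

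Confidence is high on what the plan says and that adjustment does no harm. It is only moderate on the size of the gain, which rests on assumed stratum rates, an assumed share below 32 weeks and a common odds ratio.

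**What to change.** Before outcome data are examined by group, amend the Primary outcome section so that p < 0.05 attaches to one gestational-age-adjusted analysis, either:

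- a CMH test stratified by gestational age (below 32 weeks against 32 to 33+6 weeks), or
- the logistic regression already planned, with group, gestational age and birth weight as the prespecified covariates, the last two continuous.

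Report a standardised (marginal) risk difference with 95 % CI. The adjusted odds ratio is conditional on the covariates and is not comparable with the crude 85 % against 75 % contrast on which the trial is sized. Keep the plain chi-square as a sensitivity analysis. The sample-size calculation may stay on the chi-square as a conservative basis once its own error is corrected.

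The cost is a sentence or two in a dated amendment. No new measurements and no extra infants are needed.
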